## Abstract

**Background:**

Several chronic inflammatory diseases co-exist with and accelerate sarcopenia (reduction in muscle strength, function and mass) and negatively impact on both morbidity and mortality. There is currently limited research on the extent of sarcopenia in such conditions, how to accurately assess it and whether there are generic or disease-specific mechanisms driving sarcopenia. Therefore, this study aims to identify potential mechanisms driving sarcopenia within chronic inflammatory disease via a multi-modal approach; in an attempt to help define potential interventions for future use.

**Methods:**

This prospective cohort study will consist of a multi-modal assessment of sarcopenia and its underlying mechanisms. Recruitment will target three chronic inflammatory diseases: chronic liver disease (CLD) (*n*=50), with a subset of NAFLD (*n*=20), inflammatory bowel disease (IBD) (*n*=50) and rheumatoid arthritis (RA) (*n*=50) both before and after therapeutic intervention. In addition, 20 age and sex matched healthy individuals will be recruited for comparison. Participants will undergo 4 assessment visits at weeks 0, 2, 12 and 24. Visits will consist of the following assessments: blood tests, anthropometrics, functional assessment, quadriceps muscle imaging, actigraphy, quality of life questionnaires, food diary collection and muscle biopsy of the vastus lateralis (at weeks 2 and 24 only). In addition, stool and urine samples will be collected for future microbiome and metabolomics analysis.

**Discussion:**

This is the first study to use a multi-modal assessment model to phenotype sarcopenia in these chronic inflammatory diseases. We hope to identify generic as well as disease-specific mechanisms driving sarcopenia. We appreciate that these cohorts do require separate standards of care treatments which limit comparison between groups.

**Ethics and dissemination:**

The study is approved by the Health Research Authority - West Midlands Solihull Research Ethics Service Committee Authority (REC reference: 18/WM/0167). Recruitment commenced in January 2019 and will continue until July 2021. The study was halted in March 2020 and again in January 2021 with the COVID-19 pandemic. The findings will be disseminated through peer-reviewed publications and conference presentations. All data will be stored on a secure server.

**Trial registration:**

ClinicalTrials.gov Identifier: NCT04734496

## Background

In many chronic inflammatory diseases, including rheumatoid arthritis (RA), Inflammatory Bowel Disease (IBD) and chronic liver disease (CLD) incorporating cirrhosis, loss of muscle strength, mass and physical performance (sarcopenia) is a hallmark of advanced disease, contributing to poor patient quality of life, a reduced response to challenges such as surgery or infection, and higher mortality [1]. The current working definition of sarcopenia by the European Working Group on Sarcopenia in Older People (EWGSOP) focuses on low muscle strength and either low muscle quantity or quality with poor physical performance as an indicator of severity [1, 2]. The extent of sarcopenia and the factors driving it in chronic inflammatory conditions remain poorly defined, limiting strategic or personalised therapeutic intervention.

Muscle mass is determined by the balance of protein synthesis and degradation. Anabolic signals deriving from nutrients (amino acids), physical activity and hormones such as IGF-1 and testosterone, mediate their effects through downstream targets including AKT and mTOR [3]. Catabolic signals which induce protein breakdown through induction of atrogenes such as MAFbx and MURF1, include inflammation, physical inactivity, cortisol generated in muscle via the activation of 11βHSD1 and the hormone myostatin which inhibits myoblast differentiation into mature muscle fibres and blocks AKT signalling [4–7]. The relative contribution of these mechanisms to sarcopenia in chronic inflammatory disease remains partially understood and is a major focus of this study.

### Chronic liver disease

A significant proportion of patients with CLD have a degree of malnutrition and this is closely associated with sarcopenia [8, 9]. Muscle wasting within CLD can be due to several factors including altered metabolism and inactivity. Protein-energy malnutrition is very common in patients with liver cirrhosis (estimated at 65–90%) [10]. Mechanisms reducing protein synthesis and enhancing degradation such as accelerated starvation where glycogen depletion occurs, insulin resistance and hyperammonaemia predominate in CLD [10, 11]. It is becoming increasingly clear that the degree of sarcopenia is directly related to outcomes in patients with liver disease. In a recent study of 130 patients with cirrhosis, survival at 5 years was 50% in those with sarcopenia at baseline, compared to 80% without sarcopenia at baseline [12]. In a study of 669 cirrhotic patients assessed for transplantation in Canada and the USA, sarcopenia was present in 45% of the patients and they had a median survival of 20 months compared to 95 months for those without sarcopenia [13].

In liver disease, sarcopenia may be hidden by either oedema masking muscle loss, or obesity [14, 15]. Current prognostic indicators such as the Royal Free Hospital Global Assessment (RFH GA) tool, or scoring systems such as Child-Pugh score and Model for End Stage Liver Disease (MELD) [16] score based on anthropometry/nutritional assessment of patients, may thus have reduced sensitivity in the presence of these relatively common confounders. This can underestimate the risk for those with sarcopenia and reduce the validity of assessing and prioritising patients for liver transplant surgery. In addition, since muscle mass is a static reflection of the health of the musculoskeletal system, it is also important to assess dynamic aspects such as strength, power and fatigability.

With the mounting clinical evidence of the negative impact of sarcopenia in cirrhosis, research into the underlying mechanisms is beginning to evolve. A positive anabolic effect has been observed in a small number of cirrhotic patients fed a leucine-rich preparation of amino acids [17] which suggests that cirrhotic patients should respond well to both resistance exercise and nutritional signals. Inflammation can drive muscle degradation, with inflammatory cytokines increasing activity of 11–beta hydroxysteroid dehydrogenase 1 (11βHSD1) to generate cortisol within the muscle [18] as well as promoting insulin resistance. The profound inflammatory state in cirrhosis may, therefore, be a potential driver of muscle loss.

### Inflammatory bowel disease

Sarcopenia, often included within the spectrum of malnutrition, is present in patients with IBD, including both Crohn’s disease (CD) and ulcerative colitis (UC). Malnutrition affects up to 75% and 62% of patients with CD and UC, respectively [19]. The current prevalence of sarcopenia in IBD is not fully appreciated; a recent meta-analysis found 52% of patients with CD and 37% of patients with UC have sarcopenia (as defined by low muscle mass independently) [20] with a considerable impact on quality of life.

Fatigue is a common symptom associated with IBD [21]. It is multifactorial and not necessarily associated with clinical inflammatory disease activity. Approximately 50% of patients with IBD report fatigue at the time of diagnosis [22] which can present as diminished physical activity and isokinetic muscle strength. Sarcopenia plays a role in impacting on other aspects of quality of life including a reduction in mobility, usual activities and pain/discomfort score compared with healthy controls [23]. The prevalence and clinical impact of sarcopenia in CD is poorly understood [24]. However, there are several studies that identify the negative impact of sarcopenia on post-surgical outcomes in patients with IBD, for example, increased post-operative complications. Sarcopenia can also be an independent predictor of the need for bowel resection among IBD patients [25]. There is emerging evidence of increasing obesity in patients with IBD, therefore sarcopenic obesity will likely further materialise within this cohort [20].

In relation to drivers of sarcopenia, impaired activation of muscle synthesis pathways such as the IGF1-Akt pathway may be responsible [26]. The reduction in signalling through this pathway is known to be important in the anabolic resistance of age-related sarcopenia but has not been extensively studied in IBD. A key role for inflammation as a driver of muscle wasting has been suggested by a small study which showed sarcopenia was reduced by anti-TNFα monoclonal antibody therapy [27].

### Rheumatoid arthritis

Muscle atrophy develops in two-thirds of RA patients, leading to debilitating rheumatoid cachexia which incorporates sarcopenia, shortened working life and poor quality of life [28]. As similarly reported in IBD cohorts, fatigue is a frequently reported symptom in those with RA [29]. The heightened inflammatory status of RA patients has been linked to an increase in whole-body protein breakdown [30, 31]. 11βHSD1 has been shown to be elevated in muscle from patients with RA, this may be a protective response to heightened inflammation as studies with 11βHSD1 knockout mice lacking this glucocorticoid generating enzyme developed more severe myopathy [32]. Furthermore, anti-TNFα therapy does not reverse sarcopenia, despite control of systemic inflammation, suggesting that other mechanisms are driving sarcopenia in RA [33]. The current most effective treatment to protect against sarcopenia and improve physical function in RA patients is exercise training [34]. It has been demonstrated that patients with RA are relatively sedentary with the majority of their physical activity remaining low intensity [35], however low-level physical activity can stimulate reductions in cardiovascular risk, insulin resistance and mortality [36]. In particular, a recent RCT implementing a supervised progressive resistance training in patients with RA was proven to increase muscle mass with improved function [37].

The aim of this study is therefore to determine the extent of sarcopenia in three chronic inflammatory diseases, CLD, IBD and RA, and to identify the processes, both molecular and lifestyle, contributing to sarcopenia in each disease, in order to identify common and disease-specific mechanisms. This will provide the evidence base for future studies testing interventions to reduce sarcopenia in each of these diseases.

## Methods

### Study overview

The proposed study is a single centre, longitudinal observational, prospective study of a cohort of patients with sarcopenia associated with chronic inflammatory disease, to identify generic and disease-specific mechanisms that potentially drive sarcopenia.

Patients recruited to the study will undergo several assessments (anthropometric, functional, serological, radiological, lifestyle and health-related quality of life evaluation) to assess their sarcopenia status and provide muscle biopsies on two occasions to allow further analyses including protein turnover, mitochondrial and satellite cell function, RNA sequencing, to be undertaken. Patients will be assessed at four defined time points: baseline, 2 weeks, 12 weeks and 24-week time points to allow analysis pre- and post-biologic therapy in the IBD and RA cohorts. Some of the CLD participants will undergo a liver transplant during their participation allowing a pre- and post-transplant comparison. Patients will be recruited from the University Hospitals Birmingham Foundation Trust, Birmingham, UK. Patients will continue with their standard of care management as determined by their regular specialty team. Age and sex matched healthy controls will undergo the same assessments and provide a muscle biopsy at a single study visit. They will comprise of people without sarcopenia or any significant comorbidities, with a regular level of activity (ie those without a high level of exercise/performance or not sedentary).

### Study aims

The aims of this study are:To assess the extent of sarcopenia in our three target cohorts using several methods to assess muscle mass, physical performance and strength.To identify potential mechanisms of sarcopenia in each disease through a multi-modal assessment process.To observe any longitudinal changes in each cohort over a 6-month period.

### Study design

#### Patient selection and sample

A target of fifty patients (over the age of 18 years) will be selected from:Patients with CLD, predominantly liver cirrhosis or end-stage liver disease (ESLD)) who are being assessed for liver transplantation (LT). A further twenty patients with non-alcoholic related fatty liver disease (NAFLD), confirmed by transient elastography +/− liver biopsy, with significant fibrosis (Kleiner fibrosis stages F2–F4) and without ESLD will also be identified and recruited for comparison.Patients with active IBD who are undergoing medical management only and are due to commence a new biologic treatment.Patients with active rheumatoid arthritis (RA) who are commencing a new biologic treatment.

We will also recruit an age-sex matched sample of twenty healthy individuals as a control cohort for comparison.

This is an observational prospective cohort study with deep phenotyping (experimental) of each patient group to determine the mechanisms underlying sarcopenia in each cohort, therefore a sample size calculation was not applicable. However, we calculated that 50 patients per disease group is sufficient for a Spearman correlation of ≥0.3 to reach statistical significance. Recruitment targets are also based on feasibility within the time frame of the study and based on the planned statistical analysis, described below.

#### Standard of care treatment

CLD; Patients with ESLD on a transplant waiting list undergo prehabilitation (the process of enhancing functional capacity to enable the patient to withstand a forthcoming stressor [38]). This includes physical activity and nutritional optimisation [9, 39, 40].

IBD; The British Society of Gastroenterology have clear guidelines stating when treatment with a biologic therapy is indicated and are used for moderate disease +/- failure of second-line treatment in CD and UC [41].

RA: The National Institute for Health and Care Excellence (NICE) have devised a formal guidance for drug treatment in rheumatoid arthritis. This includes those with severe disease (Disease activity score (DAS) >5.1) and failure of response with combination DMARD therapy [42–44].

#### Eligibility criteria

Eligible patients will be screened via the following criteria (Table 1). CLD patients will be selected from those who undergo assessment for liver transplantation. A Non-alcoholic fatty liver disease (NAFLD) subset will be screened and recruited from the NAFLD clinic. For IBD and RA, all patients commencing a new biologic treatment (via biologic clinic screening or biologic registry screening) will be screened prior to therapy commencement.

**Table 1 Tab1:** Eligibility criteria for participants with chronic liver disease, rheumatoid arthritis or inflammatory bowel disease

	Inclusion criteria	Exclusion criteria
**CLD, IBD and RA**	1. A formal confirmed diagnosis of their underlying chronic inflammatory condition: IBD cohort patients will have endoscopic or radiological evidence. Some of the CLD cohorts will have had a liver biopsy, serological and radiological confirmation will be sufficient. a. RA cohort, clinical, serological and radiological confirmation will be sufficient. b. Biologic therapy naïve on recruitment or commencing a new biologic if in the IBD or IA cohort. 2. Adults aged ≥ 18 years 3. Able to confirm written consent to the study 4. Biologic therapy naïve on recruitment or commencing a new biologic if in the IBD or RA cohort *Pre-existing or current use of immunosuppressant agents or Disease Modifying Antirheumatic Drugs (DMARDs) are acceptable in all cohorts.* 5. Meeting ACR (American College of Rheumatology)/EULAR (European League Against Rheumatism) 2010 or ACR 1987 Criteria for rheumatoid arthritis and starting DMARD therapy. 6. Meeting criteria of an inflammatory arthritis as per the American College of Rheumatology 7. Meeting criteria of liver cirrhosis including all Child Pugh scores from A-C as per British Association for the Study of the Liver guidance. 8. Meeting criteria for IBD as per the British Society of Gastroenterology guidance. 9. For muscle biopsy sampling (does not preclude patients from participating if they do not meet the below criteria) INR ≤ 1.6 Platelet count > 30	1. Refusal or lack capacity to give informed consent. 2. Currently enrolled in an interventional trial with active treatment for their chronic disease condition. 3. Previously undergone LT or biliary intervention in the CLD cohort. 4. Underlying or active cancer. 5. Biliary intervention if CLD 6. For Muscle biopsies only (able to continue in study): a. Obvious injury to both thighs. b. Active bleeding of site, pre-procedure, c. Abnormal observation parameters. d. Acute illness. e. INR > 1.6. f. Platelet count < 30. g. Anticoagulation which cannot be paused due to increased risk to pre-existing comorbidity. 7. For undergoing an MRI a. Pacemaker. b. Metal work inserted that is not MRI compatible or further information cannot be obtained.
**Healthy controls**	1. Adults aged ≥ 18 years. 2. Able to confirm written consent to the study. 3. No co-existing chronic inflammatory condition, cancer or significant premorbid disease pathology. 4. No suspicion or evidence of sarcopenia. 5. No previous transplantation.	1. Refusal or lack capacity to give informed consent. 2. Pregnancy. 3. Any recent acute illness or surgery requiring significant treatment or hospitalisation (within the last 12 weeks). 4. Any systemic corticosteroid use or replacement. 5. For muscle biopsies only: a. Obvious injury to both thighs. b. Active bleeding of site, pre-procedure. c. Abnormal observation parameters. d. Acute illness. e. INR > 1.6. f. Platelet count < 30. g. Anticoagulation which cannot be paused due to increased risk to pre-existing comorbidity.

#### Participant recruitment

Participants will be recruited from University Hospitals Birmingham, Birmingham, UK.

##### CLD cohort

All patients who attend the outpatient LT assessment clinic will be screened on the eligibility criteria. Patients with any degree of muscle wasting or functional decline will be invited to take part in the study. For the NAFLD cohort, we will screen all patients attending NAFLD clinic against the eligibility criteria.

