##### IBD and RA cohorts

For RA patients, the biologics registry will be screened, and eligible participants directed towards the research team. For IBD patients, potential participants will be identified from the nurse-led biologic clinic attended by those commencing a new biologic. A selection of patients may be identified by the IBD multidisciplinary meetings during discussions of standards of care.

Invitations to participate in the study will occur via face to face interaction during clinic and patient information sheets (PIS) distribution through post or email to eligible patients by the clinical research teams. We will then contact the patient up to 4 weeks after they have received the PIS to discuss their potential participation. The patient will be free to refuse to take part or withdraw from the study at any time and this decision will not affect their care.

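### Transplant-clinic CLD patients are invited on muscle wasting or functional decline, the outcome being measured, so the CLD extent of sarcopenia is biased upward by an unknown amount and is not comparable with the other cohorts

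*Protocol article*

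**What the plan says.** All quotations are from the protocol article.

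- **CLD, transplant clinic** (Participant recruitment, CLD cohort). "All patients who attend the outpatient LT assessment clinic will be screened on the eligibility criteria". The next sentence adds: "Patients with any degree of muscle wasting or functional decline will be invited to take part in the study". Table 1 has no muscle or function criterion for patients.
- **NAFLD** (same section). "For the NAFLD cohort, we will screen all patients attending NAFLD clinic against the eligibility criteria". No muscle condition.
- **RA** (IBD and RA cohorts). "For RA patients, the biologics registry will be screened, and eligible participants directed towards the research team". No muscle condition.
- **IBD** (same section). "potential participants will be identified from the nurse-led biologic clinic attended by those commencing a new biologic", with some patients found through multidisciplinary meetings. No muscle condition. The Eligibility criteria section says of both diseases that "all patients commencing a new biologic treatment (via biologic clinic screening or biologic registry screening) will be screened prior to therapy commencement".
- **Aim 1** (Study aims). "To assess the extent of sarcopenia in our three target cohorts using several methods to assess muscle mass, physical performance and strength". Experimental variables makes the degree of sarcopenia in each disease cohort a primary variable. The Statistical analysis plan section reports baseline proportions and compares disease types with unpaired non-parametric tests.
- **Study overview.** The study is called a "prospective study of a cohort of patients with sarcopenia associated with chronic inflammatory disease".
- **Caveat on comparison** (Abstract, Justification of study cohorts, Conclusion). Comparison is limited because standards of care differ. Selection on muscle status is not mentioned.

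**The concern.** Aim 1 asks how much sarcopenia there is in each disease. In the transplant clinic, being invited depends on showing signs of the condition being counted; in the other cohorts it depends on the disease and its treatment. A proportion among patients invited for wasting or decline does not estimate the proportion among transplant-assessed CLD patients, and no analysis of the enrolled patients alone can recover it. Part of any CLD excess over IBD, RA or NAFLD would then come from recruitment. Since the article's only caveat is standard of care, a reader would take that part as a disease effect.

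**Working it through.** **The plan's own figure.** The only sample-size statement is that 50 patients per disease group let a Spearman correlation of 0.3 reach significance. It reproduces: t = 0.3 × √(48 / (1 − 0.09)) = 2.18 on 48 df, p = 0.034 (two-sided 5% assumed). It has no bearing on selection.

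**Inputs for the bias**

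- p = 0.45, the prevalence of sarcopenia in cirrhotic patients assessed for transplantation (Background, Chronic liver disease). The article does not say how that study defined sarcopenia.
- Se = share of sarcopenic patients who pass the invitation rule. Not in the article; assumed 0.95.
- f = share of non-sarcopenic patients who pass. Not in the article; varied from 0.95 to 0.30.

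**Formula.** Expected prevalence among invited patients = p·Se / (p·Se + (1 − p)·f). The numerator is 0.45 × 0.95 = 0.4275. The denominator is also the share of screened patients invited.

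| f | Share invited | Expected prevalence | Bias (points) |
|---|---|---|---|
| 0.95 | 0.4275 + 0.5225 = 0.950 | 45% | 0 |
| 0.90 | 0.4275 + 0.4950 = 0.9225 | 46% | +1 |
| 0.70 | 0.4275 + 0.3850 = 0.8125 | 53% | +8 |
| 0.50 | 0.4275 + 0.2750 = 0.7025 | 61% | +16 |
| 0.30 | 0.4275 + 0.1650 = 0.5925 | 72% | +27 |

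The bias is zero only when Se = f and is upward whenever sarcopenic patients pass more often than the rest.

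**Scale.** At n = 50 the 95% CI half-width is 1.96 × √(0.45 × 0.55 / 50) = 0.138, about 14 points.

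**If NAFLD sits inside the 50.** The Abstract gives CLD n = 50 with a NAFLD subset of 20; Patient selection and sample speaks of a further twenty. If 20 of the 50 are NAFLD, 30/50 = 60% are under the rule and the pooled bias is 0.6 times the table value, whatever the NAFLD prevalence: 0.6 × 27 = 16 points at f = 0.30 and 0.6 × 8 = 5 points at f = 0.70.

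**Effect on the comparison.** Suppose true prevalence is 45% in CLD and in a comparison cohort of 50 not selected on muscle status, and every sarcopenic CLD patient passes (Se = 1). Expected CLD prevalence is then 0.45/s, where s is the share invited. The last column is the chance of a significant two-proportion test with 50 per group, none under the rule being NAFLD.

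| s | CLD prevalence | Chance of a spurious difference |
|---|---|---|
| 0.9 | 50% | 7% |
| 0.8 | 56% | 20% |
| 0.7 | 64% | 49% |
| 0.6 | 75% | 88% |

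**The case against.** **The text does not say that only such patients are invited.** True; exclusivity is inferred. It is still the natural reading, because the preceding sentence already screens all attenders and the invitation sentence would otherwise do nothing. If exclusivity is not meant, the wording needs correcting anyway.

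**The filter may be weak.** This stands as a limit on size. The rule sets no threshold, and the patients are mainly cirrhotic or end-stage and under transplant assessment. The article puts protein-energy malnutrition in cirrhosis at 65–90%. That is not the same as passing the rule, but if it were the share invited, the expected prevalence would run from 0.4275/0.90 = 47.5% to 0.4275/0.65 = 66%, a bias of about +2.5 to +21 points. A negligible bias is possible but not shown.

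**IBD and RA are selected too.** Correct. Both cohorts have active disease needing a new biologic, and that severity may relate to muscle. A reader might infer that IBD and RA are unselected samples; they are free of selection on muscle status only. Dropping the CLD rule removes one source of non-comparability, not all.

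**Enrichment suits a mechanistic study.** Reasonable for the mechanism aim, and it does not invalidate within-patient change over 24 weeks. It does not rescue Aim 1 for CLD or the contrasts of extent.

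**The overview is loosely worded.** Probably so: the same section says that patients are assessed for sarcopenia status. It needs rewording but is minor on its own.

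**Conclusion.** The concern holds for the CLD part of Aim 1 and for comparisons of extent between CLD and the IBD, RA or NAFLD patients. The stated rule conditions on the outcome in one group only, and the stated caveats do not cover it. On the natural reading the direction is upward. The size is unknown: about 0 to +27 points for patients under the rule, given 45% prevalence, an assumed 95% pass rate in sarcopenic patients and assumed pass rates of 95% down to 30% in the others; about 0 to +16 points for the pooled group if it contains the 20 NAFLD patients.

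Three stronger readings go beyond the document. A reader might infer that a material inflation is certain; it is not, because the pass rates are not given and a bias near zero lies within the range. A reader might infer that the longitudinal results are invalid; each patient is compared with himself or herself, so they are not, although selection on low function invites some regression to the mean. A reader might infer that the CLD correlations are materially weakened by a narrower range of muscle measures; that is possible in principle, but nothing in the article allows it to be quantified.

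**What to change.** Recruitment has run since January 2019 and is due to end in July 2021, with two halts, so reporting is the main remedy.

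1. **Patients enrolled under the rule.** Report screened, invited and enrolled counts where records allow. The article names no screening log, but Data management says that data are collected from when a patient is considered for entry. Label the CLD proportion as conditional on the invitation rule. Do not compare extent of sarcopenia between CLD and the other cohorts.
2. **NAFLD.** Report separately, and state whether the 20 are inside or additional to the 50.
3. **Remaining recruitment.** Invite every transplant-clinic patient eligible under Table 1, whatever the muscle status, and record whether each was enrolled before or after the change.
4. **Text.** Reconcile the Study overview, Study aims, Table 1 and CLD cohort sections. The overview should describe patients with chronic inflammatory disease. Add selection on muscle status to the stated limits on comparison.

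**Cost.** A short change to the recruitment procedure, a tally from existing records and a few sentences of reporting; the labelling and the limit on comparison need no new data. The downside is somewhat fewer severely sarcopenic CLD patients and two selection periods to report within about 50 patients.
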